## Abstract

**Background:**

Although significant progress has been made in the pharmacologic management of Parkinson's Disease (PD), effective management of movement disorders is still a hurdle for therapeutics targeting PD. Acupuncture is one therapeutic option that could potentially improve the motor function of PD and is widely used as adjuvant therapy. Among the various acupuncture approaches, *Qihuang Needling* (QHN) therapy has been found to improve motor-function control for patients with PD. However, evidence regarding its efficacy remains scarce. Therefore, to address this need, this study will determine the effects of QHN therapy on motor function in patients with PD and compare it to placebo effects.

**Methods:**

This trial is a multicenter, prospective randomized controlled clinical trial. We randomly allocated 144 participants to two groups of 72 patients. Patients in the treatment group were treated with QHN therapy. The control group had undergone insertion of acupuncture needles at sham acupoints not corresponded to acupuncture points. Participants in the verum treatment group and sham-acupuncture control group received 9 sessions over 6 weeks followed by 8 weeks of follow-up. The primary outcome was the change of motor function from baseline to weeks 6 and 14 measured by the PD Rating Scale-Part III Motor Examination (UPDRS-III). Secondary outcome measures included the change of PD daily quality of life-39 (PDQ-39) and Non-Motor Symptoms Scale for PD (NMSS) from baseline to weeks 6 and 14.

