### Trial Design

For this study, we designed a multicenter, assessor and statistician blinded, randomized controlled trial (RCT) to compare QHN therapy with sham acupuncture in patients with PD. Trials were conducted in three medical centers: the First Affiliated Hospital of Guangzhou University of Traditional Chinese Medicine, the Third Affiliated Hospital of Sun Yet-Sen University, and the Guangdong 999 Brain Hospital.

A total of 144 patients with PD were recruited and randomly assigned to either the QHN therapy group (treatment group) or sham-acupuncture group (control group) at a 1:1 ratio (Figure 1). Our study was conducted according to the Declaration of Helsinki, and the Standard Protocol Items: Recommendations for Interventional Trials (SPIRIT) checklist is given in Supplementary File 1.

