### Outcome Measurements

All outcome measurements were taken at baseline (before treatment), 6 weeks after treatment, and 14 weeks after treatment.

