### Sample-Size Calculation

This trial used a clinical-superiority design to verify that QHN therapy's effect was superior to that of sham acupuncture. The primary outcome measure was the UPDRS-III score difference before and after the treatment. According to previous research (17), assuming the standard deviation (SD) to be 8.0 and the mean of the treatment effect of the two groups to be 4.36 and 0.25, respectively, the statistical power was 80%, and the significance level was 0.05. Using PASS software requires each group to contain no <61 patients. With an estimated 15% dropout rate, we planned to recruit 72 patients for each group, for a total of 144 patients.

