### Statistical Analysis

We used mean and SD for normally distributed variables, or median (interquartile) for the variables not normally distributed, to summarize the participants' demographic, health conditions, and clinical outcomes at three different time points. Two statisticians, blinded to the group setting, analyzed the data independently *via* SPSS software (version 26.0). Missing data were imputed according to the last-observation-carried-forward (LOCF) principle. Furthermore, the data were analyzed by the intent-to-treat principle.

The normality of the variables was assessed using the normal probability plot. The continuous variables normally distributed were assessed by the student's t-test. Otherwise, the Mann-Whitney test or Wilcoxon test was applied. The Fisher's exact or the chi-square test was adopted for categorical data, and statistical significance was set at *p* < 0.05.

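### The primary time point is not fixed: weeks 6 and 14 are both primary in the abstract, the sample size covers one comparison with no week named, and no rule says which week decides

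*Protocol article*

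**What the plan says.** The protocol article describes the primary outcome in four places.

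- **Abstract, Methods:** "The primary outcome was the change of motor function from baseline to weeks 6 and 14", measured by UPDRS-III. The same paragraph sets out 6 weeks of treatment and then 8 weeks of follow-up, so week 6 is the end of treatment and week 14 the end of follow-up.
- **Outcome Measurements and Primary Outcome Measurement:** the first gives the visit times ("All outcome measurements were taken at baseline (before treatment), 6 weeks after treatment, and 14 weeks after treatment"); the second describes the scale. Neither singles out a primary time point.
- **Sample-Size Calculation:** "The primary outcome measure was the UPDRS-III score difference before and after the treatment". This is one difference with no week attached. The inputs are "assuming the standard deviation (SD) to be 8.0", "the mean of the treatment effect of the two groups to be 4.36 and 0.25, respectively" and "the statistical power was 80%, and the significance level was 0.05", which lead to 61 per group and, with 15% dropout, 72 per group.
- **Statistical Analysis:** t-tests or rank tests, with the sentence "statistical significance was set at" p < 0.05. It gives no order of testing, no split of alpha and no requirement that both weeks succeed.

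**The concern.** Week 6 asks whether the needling works by the end of treatment. Week 14 asks whether an effect persists eight weeks after it. The two answers can differ. If they do, the text does not say whether the trial has succeeded, and whichever week is significant could be reported as the primary result.

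This goes beyond a multiplicity method that could be left to an analysis plan. The abstract and the sample-size section describe the primary outcome differently. What the primary outcome is, and when it is measured, belongs in the protocol, because the sample size has to be built on it.

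The visit wording adds to the doubt. Read literally, Outcome Measurements counts from the treatment. If that means its end, the visits fall at 6 + 6 = 12 and 6 + 14 = 20 weeks from the start, and the second lies beyond the 6 + 8 = 14 weeks that the abstract describes.

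**Working it through.** **Inputs from the protocol.** Difference 4.36 − 0.25 = 4.11 points; SD 8.0; alpha 0.05; power 80%; "sham-acupuncture group (control group) at a 1:1 ratio"; dropout 15%. Sidedness is not stated. Two-sided is taken because it reproduces 61, whereas one-sided gives 47.

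**Assumptions, not in the protocol.** The correlation ρ between the week 6 and week 14 changes is shown from 0.5 to 0.9. The same difference and SD are taken at both weeks.

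**Step 1: the plan's own figure.** Normal approximation: n = 2 × [8.0 × (1.960 + 0.842) / 4.11]² = 59.5, so 60 per group. With the noncentral t distribution, power is 79.7% at 60 and 80.4% at 61, so 61 is right for a t-test. Dropout: 61 / 0.85 = 71.8, so 72. Both stated figures reproduce for one comparison.

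**Step 2: two comparisons.** Treat the two weekly test statistics (Z₁, Z₂) as bivariate normal with correlation ρ and common mean μ = 4.11 / (8.0 × √(2/n)):

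- n = 61: μ = 4.11 / 1.449 = 2.84
- n = 72: μ = 4.11 / 1.333 = 3.08

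Then:

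- Error if either week suffices = 1 − P(|Z₁| ≤ 1.96 and |Z₂| ≤ 1.96) with μ = 0
- Power if either week suffices = the same expression with μ as above
- Power if both are required = P(Z₁ > 1.96 and Z₂ > 1.96) with μ as above

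| ρ | Error, either suffices | Power, either suffices, n = 61 | Power, both required, n = 61 | Power, both required, n = 72 |
|---|---|---|---|---|
| 0.5 | 9.1% | 92% | 70% | 79% |
| 0.7 | 8.3% | 89% | 73% | 80% |
| 0.9 | 7.0% | 86% | 76% | 83% |

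When both are required, the error is at most 5%. The normal approximation is slightly generous: for one test at n = 61 it gives 81.0% against 80.4% from the t distribution.

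**Step 3: alpha split of 0.025 per week.** At 61 per group the t-test has 71.4% power for each week. The power to win at least one week, which is the success criterion that a split serves, is 86% at ρ = 0.5, 83% at 0.7 and 78% at 0.9.

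**Step 4: one week named as primary.** Error 5%, power 80.4%, and 61/72 per group stand.

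**The case against.** Four points can be made for the plan.

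*The sample-size section already implies week 6.* Its singular before/after wording most naturally means the end of treatment. This stands as the likeliest reading and supports the fix. But the section names no week, and the abstract expressly adds week 14, so the conflict remains.

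*Testing rules are commonly left to the analysis plan, and this is a condensed article.* That is fair for the order of testing or the adjustment method. It does not excuse two descriptions of the primary outcome in one document.

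*The power loss may not materialise.* Statistical Analysis plans intention-to-treat with last observation carried forward, so up to 72 per group could be analysed. One-test power would then be about 86%, and power for both weeks about 79% to 83%. This stands as an upper bound. The extra 11 per group were added to cover dropout, and carried-forward values need not show the full effect.

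*Week 14 matters to the sponsor.* The Discussion suggests that the effects of this needling may last, so making week 14 secondary is a real choice. Keeping both weeks primary is legitimate if the rule is stated and the power is restated for it.

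A reader might also infer that neither the 5% error rate nor the 80% power holds. The documents do not support that. Under the either-week rule the error rises but power exceeds 80%; under the both-weeks rule the error is controlled and only power falls. Nor is the sample size miscalculated. A much lower power follows if the effect is assumed to fade by week 14, but no figure for fading is given, and the result would mostly reflect that assumption.

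**Conclusion.** The point holds. The primary time point is inconsistent between the abstract and the sample-size section, and nothing says which week decides the trial. The consequence is conditional on the missing rule: a type I error of about 7% to 9% if either week suffices, or power of about 70% to 76% at 61 evaluable per group if both are required. These figures rest on an assumed ρ of 0.5 to 0.9 and on the full 4.11-point difference with SD 8.0 at both weeks. The direction does not change across that range. The error figures count false positives in either direction. This should be settled before unblinding, because it concerns the trial's main claim.

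**What to change.** Name one primary time point. Week 6, as the end of treatment, best fits the sample-size wording and keeps 5% error, 80% power and 61/72 per group. Make the week 14 change the first key secondary endpoint, tested at 0.05 only if week 6 is significant; this fixed sequence holds the error for the pair at 5%.

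Use the same wording in the abstract, Outcome Measurements, Primary Outcome Measurement, Sample-Size Calculation and Statistical Analysis. In the same step, reconcile the visit times under Outcome Measurements with the abstract's treatment and follow-up periods, and state from which date the weeks are counted.

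If the sponsor prefers to keep both weeks primary, state the rule for success and the power it gives. For the both-weeks rule, 80% power under the assumptions above needs 75 evaluable per group at ρ = 0.5 (75 / 0.85 = 88.2, so 89 recruited) or 67 at ρ = 0.9 (67 / 0.85 = 78.8, so 79 recruited).

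**Cost.** Naming week 6 adds no patients and no visits. It requires a protocol and registry amendment before unblinding, and week 14 alone could no longer make the trial positive.

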**Discussion:**

The results of this trial will generate data to improve our general understanding of the efficacy of QHN therapy on motor function in patients with PD and thoroughly compare these responses to the placebo effect.

**Trial Registration:**

The trial was registered at the Chinese Clinical Trials Registry (ChiCTR- 2000030871) on 16 March 2020.

## Background

Parkinson's disease (PD) is a progressive neurodegenerative condition in which patients present clinical motor symptoms, such as bradykinesia, rigidity, resting tremor of distal extremities, and postural instability (1). Additionally, patients with PD may develop a series of non-motor symptoms, such as depression, cognitive impairment, sleep disorder, and autonomic disturbance (2). Unfortunately, PD has become the second-most common neurodegenerative disorder that affects estimated 6 million people worldwide (3).

The core pathological changes of PD lie in intracellular inclusions containing aggregates of α-synuclein and striatal dopamine deficiency induced by the loss of neurons in the substantia nigra. With the discovery of the role of dopamine deficiency in PD, pharmacologic dopamine substitution treatment became the foundation of current drug therapies for PD (4). In addition to oral medications, surgical intervention, such as deep brain stimulation, has been beneficial to patients with troublesome motor fluctuations and dyskinesia due to the advanced stages of PD. However, there remain challenges in developing effective treatment options for PD with these advancements. Due to none of these treatments effectively modifies disease progression and/or delay disability, patients with PD can often suffer from progressive degeneration of motor function. As the benefits of medications wane over time with disease progression, effective management of tremor, gait, balance, posture, and dexterity are major challenges for therapeutics designed for PD movement disorders (5). Beyond these unmanaged motor symptoms, many non-motor symptoms add considerably to the overall burden of the disease (6).

Acupuncture has existed for over 4,000 years as one of the main treatments of traditional Chinese medicine. As an adjuvant therapy, acupuncture is widely used in the treatment of PD, particularly in East Asia (7). Numerous clinical trials have shown that acupuncture could improve motor symptoms and the quality of sleep, reduce the dose and frequency of anti-PD drugs, and alleviate their side effects (8–11). However, none of these studies could verify whether the benefits are due to the efficacy of the treatment or as a result of the placebo effect (12, 13).

The different operating modes of acupuncture can be divided into manual acupuncture (MA) and electroacupuncture (EA). Based on the preliminary clinical observation, *Qihuang Needling* (QHN, a kind of MA technique based on traditional meridian theory) therapy has shown promising benefits targeted against better control for PD. However, the evidence for its efficacy remains scarce. Therefore, to address this gap, we aim to investigate the efficacy of QHN therapy when compared with sham acupuncture in patients with PD.

### Trial Design

For this study, we designed a multicenter, assessor and statistician blinded, randomized controlled trial (RCT) to compare QHN therapy with sham acupuncture in patients with PD. Trials were conducted in three medical centers: the First Affiliated Hospital of Guangzhou University of Traditional Chinese Medicine, the Third Affiliated Hospital of Sun Yet-Sen University, and the Guangdong 999 Brain Hospital.

A total of 144 patients with PD were recruited and randomly assigned to either the QHN therapy group (treatment group) or sham-acupuncture group (control group) at a 1:1 ratio (Figure 1). Our study was conducted according to the Declaration of Helsinki, and the Standard Protocol Items: Recommendations for Interventional Trials (SPIRIT) checklist is given in Supplementary File 1.

**Figure 1 F1:**
[figure not shown]
Trial flow chart.

### Inclusion Criteria

The inclusion criteria in this study are as follows: (1) patients with PD, (2) patients of the age of 40–80 years old, (3) patients with a duration of PD of more than 1 year; (4) modified Hoehn-Yahr (HY) grades from 1 to 4; (5) patients who needed to take a stable dose of anti-PD drugs for more than 2 months, if treated with anti-PD drugs, or patients who had not received anti-PD medication for more than 2 months; (6) had clear consciousness and stable vital signs; and (7) patients who fully understood the study protocol and signed the consent form.

### Exclusion Criteria

Patients with any of the following criteria were excluded: (1) patients with severe hepatorenal disease, blood disease, tumor, endocrine disease, and/or infection. (2) Those who participated in other clinical trials during the same period; (3) patients with schizophrenia or other mental disorders that affected the compliance of patient; (4) those who were deaf or had communication difficulties caused by dementia; and (5) those who had a history of alcohol or drug abuse.

### Recruitment

Participants were recruited by advertisements on bulletin boards located at the Department of acupuncture and the Department of Neurology at the First Affiliated Hospital of Guangzhou University of Chinese Medicine, Guangdong 999 Brain Hospital, and the Third Affiliated Hospital of Sun yet-sun University. An independent assessor working in these departments was responsible for screening and registering the participants that met this study's inclusion criteria. The details of the participants were conserved by the Data Monitoring Committee (DMC) to ensure patient confidentiality.

### Randomization and Allocation Concealment

Central randomization was performed by the College of Acupuncture and Rehabilitation, Guangzhou University of Traditional Chinese Medicine. The random assignment operation was programmed and executed by using the SAS9.2 software. An independent researcher received the random numbers and group assignment after inputting the patients' information through an online application.

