### Interventions

To ensure the participants' safety and compliance and fulfill ethics necessities, we followed the recommendation of the Chinese Guidelines for the management of patients with PD (14). All participants in two groups received Madopar, whose dosage was recorded in detail. The original drug solutions and dosage were changed if the patients had already taken the anti-Parkinson's medicine before recruitment. In some cases, if the medications needed to be altered, the details were recorded carefully, such as the drug's name, administration time, and dosage. The whole treatment was carried out by licensed acupuncturists who had more than 5 years of clinical experience.

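### Untreated and stably treated patients both enter and all receive Madopar, but the stated primary comparison has no term for drug status at entry, which can cost precision

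*Protocol article*

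**What the plan says.** **Who enters.** Criterion 5 (protocol article, Inclusion Criteria) has two branches. One is "patients who needed to take a stable dose of anti-PD drugs for more than 2 months, if treated with anti-PD drugs"; the other is "patients who had not received anti-PD medication for more than 2 months".

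**What they take.** Interventions: "All participants in two groups received Madopar, whose dosage was recorded in detail". The same section adds: "The original drug solutions and dosage were changed if the patients had already taken the anti-Parkinson's medicine before recruitment". No start date for Madopar is given.

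**How they are allocated.** Trial Design gives the "sham-acupuncture group (control group) at a 1:1 ratio". Randomization and Allocation Concealment describes central assignment through an online application that takes patient information first, and says "The random assignment operation was programmed and executed by using the SAS9.2 software". Strata are not mentioned either way.

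**How the trial is sized.** Sample-Size Calculation: "The primary outcome measure was the UPDRS-III score difference before and after the treatment". It takes one SD of 8.0 from previous research and "the mean of the treatment effect of the two groups to be 4.36 and 0.25, respectively", with 80% power at the 0.05 level. The result is 61 per group, or 72 after 15% dropout. The drug status of the earlier study's patients is not described.

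**How it is analysed.** Statistical Analysis names Student's t-test for normally distributed continuous variables and Mann-Whitney or Wilcoxon otherwise. No covariate is named.

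**The concern.** Taken together, the Inclusion Criteria and Interventions sections describe a sample in which some patients resume or begin levodopa as trial participants while others arrive already treated. The first kind can show a UPDRS-III change due to the drug, and that change falls within the baseline-to-week-6 and week-14 window of the primary outcome. Drug status is known before randomisation, so it can be used as a design or analysis factor.

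A two-sample test without that factor treats the between-status difference as noise. If the noise was not in the 8.0 used for planning, the trial has less than its stated power. In any one trial, a chance excess of starters in one arm also moves the observed difference, and an unadjusted test does nothing to correct it.

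The planned sham change of 0.25 points raises a related question. It is close to zero, which is hard to picture in an arm where part of the patients start levodopa, unless the source population was different.

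**Working it through.** **1. Reproduce the plan's figure.** Inputs from Sample-Size Calculation: difference 4.36 − 0.25 = 4.11; SD 8.0; alpha 0.05 (sidedness not stated); power 80%.
- Two-sided t-test (noncentral t): 60 per arm gives 79.7%, 61 gives 80.4%, so n = 61, as stated.
- A one-sided test would need only 48, so the plan is two-sided.
- Dropout: 61 / 0.85 = 71.8, so 72 per arm, as stated.

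The sizing arithmetic is correct.

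**2. Add the mixture.** Let p be the share of starters and D their extra UPDRS-III improvement, equal in both arms. Neither is in the article, so both are assumptions: p = 10–30%, D = 5–10 points. Suppose also that 8.0 is the SD within each drug-status group. Then

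SD = √(8.0² + p(1 − p)D²)

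| p | D | added variance | SD | power, 61 per arm | power, 72 per arm |
|---|---|---|---|---|---|
| 0.1 | 5 | 2.25 | 8.14 | 79.0% | 85.3% |
| 0.2 | 5 | 4.00 | 8.25 | 78.0% | 84.4% |
| 0.3 | 5 | 5.25 | 8.32 | 77.2% | 83.7% |
| 0.1 | 10 | 9.00 | 8.54 | 75.0% | 81.8% |
| 0.2 | 10 | 16.00 | 8.94 | 71.1% | 78.2% |
| 0.3 | 10 | 21.00 | 9.22 | 68.5% | 75.7% |

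Without the mixture, power is 80.4% at 61 and 86.5% at 72. The last column applies if all 72 are analysed, as intention-to-treat with last observation carried forward implies; it ignores any dilution from carrying values forward.

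If 8.0 already comes from a similarly mixed population, nothing is added and the stated power stands.

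**3. Error rate and bias.** Simulation of the unadjusted t-test at 61 per arm, 40,000 trials per setting:
- p = 0.2, D = 5: type I error 5.1%; mean estimate 4.13 for a true 4.11.
- p = 0.3, D = 10: type I error 5.0%; mean estimate 4.10.

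The test remains valid.

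**4. Chance imbalance.** With 29 starters (20% of 144) split at random over 72 and 72, the arms differ by 9 or more with probability 0.095, counting both directions. A difference of 9 shifts the estimate by (9/72) × D: 0.63 points at D = 5, or 1.25 at D = 10. The planned standard error is 8.0 × √(2/72) = 1.33, so even 1.25 is less than one standard error.

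**5. The sham change.** Expected sham change = 0.25 + pD: from 0.25 + 0.1 × 5 = 0.75 to 0.25 + 0.3 × 10 = 3.25 points. The active mean rises by the same pD, so the planned difference of 4.11 does not change.

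**The case against.** The strongest reply has four parts.

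- **Randomisation.** A reader might infer from the SAS sentence that allocation ignored drug status. The article does not support that. It names no strata, but it does not say there are none, and patient information is entered before assignment, which is compatible with stratifying. A journal article commonly leaves such detail to the full protocol. This part of the reply stands in full.
- **The SD.** A reader might also infer that starters inflate the SD of 8.0. That would require the earlier study to exclude such a mix, and the article does not say so. The share of starters and their response are likewise unsourced. This stands; the power figures are conditional.
- **Imbalance and the sham mean.** Chance imbalance is not bias, since the standard error already allows for it. With equal responses in both arms, the 0.25 has no effect on n. Both stand.
- **The two groups are less clean than they look.** More than 2 months without drugs does not mean never treated, and no start date for Madopar is given. Prior regimens are also said to have been changed, so treated patients may have drug-related change too. This stands, and it means that a factor for entry status may not remove all the drug-related variance until the text is reconciled.

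What the reply does not remove is the stated method. The article admits both kinds of patient, gives all of them Madopar, and names a comparison with no term for the difference. Madopar dosage is recorded, but no stated analysis uses it.

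**Conclusion.** The point holds as a matter of precision. On the text as written, a source of UPDRS-III change that is known at entry is left in the error term of the primary comparison. Validity is not at issue: the estimate is unbiased and the type I error is kept.

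The size depends on three things the article does not give: the share of starters, their extra response, and whether 8.0 already contains the mix. If it does not, the loss at 61 per arm is about 1 to 3 percentage points at a 5-point response, and up to about 12 points (80.4% to 68.5%) at 30% starters with a 10-point response. If it does, the stated power is unaffected, although adjustment could still gain precision.

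The 0.25-point sham change is a reason to describe the source population. It is not a sizing error.

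**What to change.** 1. **Statistical Analysis.** Replace the unadjusted primary comparison with a linear model (ANCOVA) of UPDRS-III that includes treatment, anti-PD drug status at entry and baseline UPDRS-III.
2. **Randomization.** State whether assignment is stratified by drug status at entry. If it is not, add that field to the online randomisation.
3. **Sample-Size Calculation.** State the medication status of the population behind the 8.0 SD and the 0.25-point sham change, and say that 80% power is conditional on a residual SD of 8.0.
4. **Inclusion Criteria and Interventions.** Reconcile the stable-dose requirement with the sentence that prior regimens were changed, so that the drug-status factor is well defined. Which clinical rule applies is for the trial team to settle.

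The cost is small: model terms, at most one field in an existing system, and a few sentences, with no added patients or visits. The downside is that a model replaces a simple t-test. The adjustment can be made even if recruitment has begun.
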